## Abstract

**Background:**

Posterior Heel pain can present in children of 8 to 14 years, associated with or clinically diagnosed as Sever's disease, or calcaneal apophysitis. Presently, there are no comparative randomised studies evaluating treatment options for posterior heel pain in children with the clinical diagnosis of calcaneal apophysitis or Sever's disease. This study seeks to compare the clinical efficacy of some currently employed treatment options for the relief of disability and pain associated with posterior heel pain in children.

**Method:**

Design: Factorial 2 × 2 randomised controlled trial with monthly follow-up for 3 months.

Participants: Children with clinically diagnosed posterior heel pain possibly associated with calcaneal apophysitis/Sever's disease (n = 124).

Interventions: Treatment factor 1 will be two types of shoe orthoses: a heel raise or prefabricated orthoses. Both of these interventions are widely available, mutually exclusive treatment approaches that are relatively low in cost. Treatment factor 2 will be a footwear prescription/replacement intervention involving a shoe with a firm heel counter, dual density EVA midsole and rear foot control. The alternate condition in this factor is no footwear prescription/replacement, with the participant wearing their current footwear.

Outcomes: Oxford Foot and Ankle Questionnaire and the Faces pain scale.

**Discussion:**

This will be a randomised trial to compare the efficacy of various treatment options for posterior heel pain in children that may be associated with calcaneal apophysitis also known as Sever's disease.

**Trial Registration:**

Trial Number: ACTRN12609000696291

Ethics Approval Southern Health: HREC Ref: 09271B

## Introduction

Calcaneal apophysitis (also known as Sever's disease [1]) is an overuse syndrome thought to be caused by repetitive micro trauma due to increased traction of the calcaneo-achilles apophysis [1-3]. This condition is characterised by pain experienced near the lower posterior aspect of the calcaneus in close proximity to the attachment of the Achilles tendon into the secondary growth plate of the calcaneus. The calcaneal growth centre or apophysis appears at approximately seven years of age [4] and fuses in girls of age approximately thirteen years and boys of fifteen years [2,5,6], hence this condition is typically seen in pre-adolescent and adolescent children. Posterior heel pain reportedly associated with Calcaneal apophysitis has been reported to comprise 2%-16% of musculoskeletal injuries in children [2,7,8].

Several theories regarding the pathomechanics of posterior heel pain associated with calcaneal apophysitis in children have been proposed and can be categorised into the following:

1. Growth and gastrocnemius/soleus tightness: The presentation of calcaneal apophysitis is thought to be due to a period of rapid growth. The rapid period of growth caused increased relative tension in the Achilles tendon/triceps surae complex which amplifies traction on the apophysis [2,3,9].

2. Biomechanics: It has previously been suggested that children with cavus or planus foot types are more susceptible to calcaneal apophysitis possibly due to a harder heel strike placing increase strain on the affected area [10-12].

3. Infection: Previous authors have reported infection to have directly caused calcaneal apophysitis [10,13], though other authors have listed infection as a differential diagnosis [3,10,11,14].

4. Trauma: Repetitive or single traumatic incidents have been anecdotally reported to be the causes of posterior heel pain in calcaneal apophysitsis [15-17]. There is limited evidence to support this hypothesis.

5. Obesity: In children obesity has been observed as an influential factor in calcaneal apophysitis [1,6,18].

Despite the presence of these theories, there has been limited clinical data presented to support them to date.

Recommend treatment paths for posterior heel pain clinically diagnosed to be associated with calcaneal apophysitis are varied with most publications relying upon earlier study recommendations [19]. Treatment recommendations have included: rest or cessation of sport [3,20,21], use of heel lifts [2,22,23], use of mobilisation [1,2,22], orthoses [21,22,24], stretching or strengthening [20,21,24], padding for shock absorption/strapping of heel [24-26], ultrasound/pharmaceutical prescriptions/ice [20,21,27], immobilisation casting or crutches [23,26,28] or removal of apophysis [29]. A recent literature review concluded that due to no valid or reliable data being available regarding calcaneal apophysitis causation and no clinical trial comparing treatment approaches, no clinical treatment path can be determined as "best practice" [19], therefore further research into treatment options is required.

This study aims to compare two clinically applied treatment options for the management of posterior heel pain associated with the clinical diagnosis of calcaneal apophysitis.

## Method

### Study Design

This is a factorial randomised controlled trial; two factors (shoe orthosis and footwear) each with two levels (heel raise/pre-fabricated orthoses and current footwear/new athletic footwear respectively), with a three month follow-up period. A consort flow chart for the design of this study is presented (Figure 1). There is no control group due to this clinical trial being conducted within a health setting. The trial is also being conducted within a lower socioeconomic catchment and it is well documented that there is lower participation in sporting activities [30] and higher rates of obesity [31,32] in these areas. It was decided that there was a risk of participant's not re-starting physical activity should there be a cessation of sport group.

**Figure 1 F1:**
[figure not shown]
**Consort flow chart for the study**.

### Participants and Setting

Children aged between eight and fourteen years will be recruited from the case load of podiatrists at Cardinia Casey Community Health Service and Peninsula Health Service. Patients will be eligible to participate if they provide a subjective report of pain located at the calcaneal apophysis (i.e., posterior aspect of heel) with pain on palpation (positive calcaneal squeeze medial and lateral borders), have not in the last 12 months been diagnosed fracture or tumour of the foot or leg and have not been diagnosed with infective, reactive or rheumatoid arthritis.

### Interventions

#### Minimum care for all participants

All participants will receive a standardised icing and stretching program. The participants will be asked to ice for 10 minutes a day, during the initial stage of treatment (one month). The icing treatment will continue only after sporting activities until the participant is pain free. The stretching program will be initiated after the acute phase of calcaneal apophysitis. The stretch will be an isometric weight-bearing gastrocnemius stretch.

#### Factor 1: Shoe orthoses

The two levels of shoe orthoses to be investigated are:

1. Heel raise (Figure 2)

**Figure 2 F2:**
[figure not shown]
**Heel raise shoe orthoses**.

2. Prefabricated orthoses (Figure 3).

**Figure 3 F3:**
[figure not shown]
**Prefabricated shoe orthoses**.

Both of these interventions represent widely available, mutually exclusive treatment approaches that are relatively low in cost compared to customised foot orthoses. Heel raises (Figure 2, 6 mm heel raise) are made from high density ethylene vinyl acetate (EVA). The EVA heel raise is designed to reduce the activity of the gastrocnemius-soleus-achilles tendon complex on the calcaneo-achilles attachment by elevating the calcaneus [33]. Heel raises have been found to provide therapeutic relief in tendoachilles bursitis, tenosynovitis of Achilles tendons, and postoperative management of ruptured Achilles tendons [33]. The prefabricated orthoses (Figure 3, Prothotic: Firm) intervention is a firm prothotic. The prothotic is a polyurethane device that is thought to limit pronation by inverting the rear foot with medial varus wedging combined with a small notch in the cuboid area [34]. The authors have anticipated that the use of a medical varus wedging device is contraindicated with a FPI equal or less than -1. Should the child present with a FPI equal or less then that the child will be excluded from the study and offered alternative treatment through the health service. The orthoses will be covered in a 2 mm blown multi-density EVA cover (Multiform) which is anticipated to provide shock absorption. There is currently no literature on the effectiveness of any custom, semi-custom or prefabricated orthotic device in the treatment of posterior heel pain associated with calcaneal apophysitis [35].

#### Factor 2: Footwear

The two levels of footwear to be investigated are:

1. Current footwear worn by participant

2. New athletic footwear provided by study.

The first condition in this factor entails no direction for modification of current footwear being provided by the treating podiatrist. Participants will be requested to continue wearing their most commonly worn footwear. This may be school shoes, sports shoes or casual shoes dependent on the patient.

The alternate condition is the new athletic footwear prescription/replacement intervention. This involves provision of a shoe with a firm heel counter, dual density EVA midsole and rear foot control provided by adidas Australia. All shoes provided will be the same model. The footwear replacement intervention will be provided to the participant at no cost. All participants within this group will be given standardised shoe wearing in instructions. Schools within the study area allow the students to wear athletic footwear as the chosen footwear style therefore compliance with school uniform, sport and play is not anticipated to be an influencing factor. Should an issue arise; the treating podiatrist will give a letter of support for the footwear choice and liaise with the school if required.

### Instrumentation

The primary outcome measure for this study is the Oxford Foot and Ankle Questionnaire [36]. This scale measures the disability associated with foot and ankle problems in children aged from 5-16 years. This assessment is taken from the perspective of both the child and the parents and contains "physical" (6 items, Cronbach's alpha = 0.92, parent-child intraclass correlation coefficient (ICC) = 0.72), "school and play" (4 items, Cronbach's alpha = 0.89, parent-child ICC = 0.73) and "emotional" (4 items, Cronbach's alpha = 0.86, parent-child ICC = 0.72) domain areas [36].

Secondary outcome measurements will be the Faces pain scale [37,38] and the Lunge Test [38]. The Faces pain scale is a seven point verbal rating scale that will be used to measure severity of pain at rest, on palpation, during activity and after activity (2 hours post) [36,37]. The test-retest reliability data for six-year-old children yielded a rank correlation coefficient of 0.79, indicating that the scores obtained using the faces pain scale are adequately reproducible over time. Inter-rater reliability produced a high rank correlation coefficient of 0.82 [37].

The Lunge Test [39] is a clinical measure of ankle dorsiflexion. All participants will be given a standardised stretching program; measurement of the lunge test will be recorded to determine any change in ankle dorsiflexion. Intra-rater reliability of experienced raters conducting this test has been shown to be high when using a digital inclinometer (average ICC = 0.88, average 95% limits of agreement = -6.6° - 4.8°) and the clear acrylic plate (average ICC = 0.89, average 95% limits of agreement = -7.2° - 4.3°) to assist with measurement [39]. The intra-rater reliability of an inexperienced rater has also been demonstrated to be good to high when using a digital inclinometer (ICC = 0.77, 95% limits of agreement = -9.1° - 8.3°) and a clear acrylic plate apparatus (ICC = 0.89, 95% limits of agreement = -8.1° - 4.6°) to assist in measurement. Inter-rater reliability for inexperienced raters has also been found to be high for when using either the digital inclinometer (ICC = 0.95, 95% limits of agreement = -5.7° - 5.7°) and the clear acrylic plate apparatus (ICC = 0.97, 95% limits of agreement = -4.7° - 4.7°) [39].

Demographic data, including participant age, gender, height standard deviation and weight standard deviation, will be collected for all participants at the baseline assessment along with the Foot Posture Index-6 (FPI-6), a clinical standardised measure of a participant's standing foot posture [40]. This assessment allows for biomechanical factors to be examined, which has been suggested throughout the literature as a possible causative factor of calcaneal apophysitis.

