### Analysis

The intervention factors will be examined over time on the primary and secondary outcome measures using Generalised Estimating Equations. This approach is suitable for analysis of longitudinal data and has been shown to produce unbiased effect estimates with appropriate precision in the presence of missing data (missing completely at random, missing at random or missing not at random) without the need for data imputation techniques and does not involve list wise deletion of participant data where missing data is present [41]. The analysis will be undertaken to examine the main effects of the two intervention factors, however, if a significant "shoe orthoses by footwear" interaction term is identified, simple effects will be focused upon. The analysis will follow the intention-to-treat principle.

A follow-up per-protocol analysis will be conducted to account for participants who do not adhere to their allocated treatment protocol. However, such analyses will be described as being exploratory and will not be the focus of the resulting manuscript

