### Sample size

It is considered that a minimum clinically important change in the Oxford Ankle Foot Questionnaire in any domain is 7 points and that based on previous work, the maximum standard deviation in any domain is 6 points [36]. Given this experiment has 1 pre-intervention measure and 3 post-intervention measures, a sample size of n = 27 per factorial trial cell (i.e., total trial n = 108) will have >90% power to detect a significant difference of 7 points in any simple contrasts undertaken, assuming a correlation between assessment points within individual participants is r = 0.7. To account for 15% drop outs and incomplete assessments, a total of n = 124 will be recruited.

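### The primary outcome is a questionnaire that yields six scores, and none of them is named as primary

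*Protocol article*

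**What the plan says.** Under Instrumentation the protocol article states: "The primary outcome measure for this study is the Oxford Foot and Ankle Questionnaire". It then describes the instrument as having three domains, each with its own Cronbach's alpha and parent-child agreement, and says that "This assessment is taken from the perspective of both the child and the parents". The agreement for the physical domain is given as "parent-child intraclass correlation coefficient (ICC) = 0.72"; the other two domains have 0.73 and 0.72.

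Under Sample size, the target difference and the spread are set for all domains alike: "a minimum clinically important change in the Oxford Ankle Foot Questionnaire in any domain is 7 points" and "the maximum standard deviation in any domain is 6 points".

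Under Analysis: "The intervention factors will be examined over time on the primary and secondary outcome measures using Generalised Estimating Equations". Two factors are in play: "The analysis will be undertaken to examine the main effects of the two intervention factors". If the interaction between them is significant, the focus moves to simple effects.

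The article does not define a total score, choose a domain or reporter as primary, or give a significance level.

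**The concern.** A primary outcome should be one variable, or a stated set of variables with a stated rule for combining them. Here it is an instrument: three domains times two reporters gives six scores, and two factors give up to twelve main-effect tests that could each be called primary.

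Two things are at stake. If neither treatment factor does anything, the chance that at least one of these tests comes out significant is well above the nominal level. And if the scores disagree, for example if parents report a physical gain and children do not, the plan gives no basis for saying which answer is the trial's answer. The article's Conclusion expects the results to carry considerable weight in guidelines and care, so the headline score should not be open to choice after the data are seen.

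**Working it through.** **Inputs from the protocol article.** Three domains, two reporters and parent-child ICC 0.72 to 0.73 (Instrumentation); two factors (Analysis); 27 per cell, difference 7, SD 6, r = 0.7 between assessments, power above 90% (Sample size).

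**Assumptions, because the article gives no figure.** Two-sided 5% for each test; each of the six scores tested separately; correlation between domains from 0 to 0.9; the ICC used as the correlation between the child and parent test statistics; the two factors' tests treated as independent.

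**Step 1: the plan's own power figure.** For a 27-versus-27 simple contrast on a single post-treatment measure, the standardised difference is 7 / (6 × √(2/27)) = 4.287. Power is Φ(4.287 − 1.960) = Φ(2.327) = 99.0%. Averaging three post measures at r = 0.7 multiplies the variance by (1 + 2 × 0.7)/3 = 0.80 and gives 99.8%. The stated figure of more than 90% is reproduced, with room to spare.

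**Step 2: upper bound if all tests were independent.** Six tests: 1 − 0.95^6 = 26.5%. Twelve tests: 1 − 0.95^12 = 46.0%. The stated parent-child agreement contradicts independence, so this bound is not the estimate.

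**Step 3: allowing for correlation.** Six normal test statistics per factor were simulated with parent-child correlation 0.72 within a domain and correlation ρ between domains. The correlation between one reporter's score in one domain and the other reporter's in another was set either to 0.72ρ or to the smaller of ρ and 0.72; ranges below span the two choices. With p the per-factor chance, both factors together give 1 − (1 − p)².

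| ρ between domains | Per factor (6 scores) | Both factors (12 tests) |
|---|---|---|
| 0 | 23% | 40% |
| 0.3 | 22% | 38-39% |
| 0.5 | 19-20% | 35-36% |
| 0.7 | 16-17% | 30-32% |
| 0.8 | 15-16% | 28-29% |
| 0.9 | 13% | 25% |

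Check at ρ = 0: 1 − (1 − 0.227)² = 40%. If only one reporter were analysed (three domains, two factors), the range across both factors is 16-27%.

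**Step 4: after the fix.** One score gives 5% per factor and 1 − 0.95² = 9.75% across both. If all six stay primary, the most demanding Holm step uses 0.05/6, with critical value 2.638. Power for the 27-versus-27 contrast on a single post measure is Φ(4.287 − 2.638) = 95.0% by the normal approximation, or about 93% with the t distribution. For a main effect (54 versus 54) the standardised difference is 7 / (6 × √(2/54)) = 6.062, and power exceeds 99.9%.

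**The case against.** Several points on the other side are sound.

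- **The article does not say that six scores are each tested at 5%.** It gives no alpha and says only that the factors are examined on the outcome measures. Significance level, scoring and multiplicity rules are commonly left to an analysis plan, which is not shown, so their absence is no finding. This stands, and it makes the error rates conditional. It does not remove the point, because which variable is primary is for the protocol to settle, and the article settles it on something that is not one variable.
- **The wording on any domain concerns sizing.** Applying one minimum important change and the largest SD to every domain ensures that each is adequately powered. A reader might infer a success rule under which a win in any one domain counts. The text does not say that. It shows only that no domain is set above the others.
- **A reader might quote 46%.** That needs twelve independent tests, and the stated ICC of 0.72 to 0.73 rules this out; about 40% is the ceiling even with unrelated domains. Nor is about 30% a floor, since strongly correlated domains give about 25%.
- **The two factors are separate treatment questions.** Controlling error within each is a common choice in a factorial trial, so the per-factor figure is the fairer one. Even a single pre-specified score gives 9.75% across both.
- **A reader might add selection among the three visits.** The plan is a longitudinal model over all assessments, not three separate visit tests, so that addition is not supported.

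**Conclusion.** The point holds in this form: the primary outcome is not reduced to one score, and nothing in the protocol article says which of the six carries the conclusion. If each were tested at an assumed two-sided 5%, the chance of at least one false-positive primary result would be about 13-23% per factor, roughly 2.5 to 4.5 times nominal, or about 25-40% across both factors. These figures rest on separate testing of each score and on a between-domain correlation that the article does not give. The tests that follow a significant interaction ("interaction term is identified, simple effects will be focused upon") are not counted. The documents do not support saying that the plan intends to claim success on any one score, or that it has fixed a 5% level for each. The undefined primary score is certain; its size depends on the assumptions above.

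**What to change.** Before outcome data are examined by allocated group, name one domain and one reporter as the primary score, and one GEE contrast per factor, for example the main effect averaged over the three follow-ups. Make the other five scores secondary. The choice of domain and reporter is for the investigators to justify on clinical grounds. The reliability figures in the article do not decide it: they concern internal consistency and agreement, and the alphas are not attributed to either reporter.

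If all six scores are to remain co-primary, say so and apply Holm across the six within each factor, with the significance level stated.

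The cost is wording, plus fewer routes to a significant primary result. With 27 per cell, 7 points and SD 6, power at 0.05/6 remains above the stated 90%, so neither option needs a larger sample.

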#### Compliance measures

Participants will be asked to complete a star chart or star sticker placement within their school diary to daily log compliance with allocated shoe insert intervention/footwear and record days of ice application and stretching.

### Procedure

All patients presenting to the study locations with heel pain will be screened for study eligibility by their treating podiatrist. The parents of patients who meet the study inclusion criteria will be provided with a written and verbal explanation of the study, and will be asked to provide consent for their child to participate. Those for whom consent to participate is provided will have baseline assessments undertaken prior to randomisation so the assessor is blinded to participant group allocation at this time.

Randomisation will then be undertaken using a permuted-block randomisation approach stratified by site. Randomisation blocks of four or eight participants will be generated and randomly selected and the resultant allocation order will be entered into opaque, sealed envelopes for each site. An investigator not involved in recruitment or assessment of participants ([name]) will be responsible for preparing the random allocation sequence and envelopes. The treatment conditions will be provided as per the random allocation sequence following completion of the initial assessment.

As remote randomisation is not feasible, a set of tamper- evident envelopes will be provided to each participating site. The envelopes will look identical, and each will have the trial indication and a sequential number on it. The envelopes will be opaque and well sealed and the sequence of opening the envelopes will be monitored regularly by a non participating staff member who will be responsible for storing and issuing the concealed allocation envelopes. As there is no off site randomisations there is potential for bias, the authors have attempt to mitigate this concern by having the randomisation kept in a secure location

Primary and secondary outcome measurements will be undertaken at initial presentation and at one, two and three month follow-up appointments, a tolerance of +/- 1 week will be universally applied. These review appointment dates are routinely employed for this patient population and do not represent a departure from standard practice. Pre-appointment reminder text message will be employed to promote re-attendance at follow-up appointments. If a participant does not re-attend a follow-up appointment, the trial podiatrist will telephone the participant to attempt to reschedule the appointment. In the case of non-attendance, the Oxford Foot and Ankle Questionnaire will be posted with a reply-paid, addressed envelope. In the case of non-return of the questionnaire, a telephone consultation will be provided to offer completion of this questionnaire.

If a participant's pain does not resolve in the three month treatment trial an individualised podiatric assessment and treatment will be offered.

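### When a missed visit cannot be rescheduled, only the Oxford questionnaire is recovered, although three of the four Faces pain ratings could be collected by the same post and telephone route

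*Protocol article*

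**What the plan says.** All outcomes share one schedule. The Procedure section states: "Primary and secondary outcome measurements will be undertaken at initial presentation and at one, two and three month follow-up appointments". It allows a tolerance of one week either side and a reminder text before each appointment.

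For a missed appointment it sets out three steps:

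1. Rescheduling: "the trial podiatrist will telephone the participant to attempt to reschedule the appointment".
2. Post, if the child still does not attend: "In the case of non-attendance, the Oxford Foot and Ankle Questionnaire will be posted with a reply-paid, addressed envelope".
3. Telephone, if the form is not returned: "a telephone consultation will be provided to offer completion of this questionnaire".

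Steps 2 and 3 name one instrument only.

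On the pain outcome, the Instrumentation section classes the Faces scale as secondary, together with the Lunge Test. It says "The Faces pain scale is a seven point verbal rating scale" and lists four ratings: at rest, on palpation, during activity, and two hours after activity. The Conclusion describes the scale as self-report, like the primary outcome. The abstract gives the trial's outcomes in one line: "Outcomes: Oxford Foot and Ankle Questionnaire and the Faces pain scale".

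**The concern.** The abstract gives the purpose of the trial as relief of both disability and pain. The fallback for missed visits protects the disability measure and leaves the only dedicated pain measure without cover, although an envelope and a call are already planned and most of the pain measure needs no examiner.

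Attendance may well depend on pain: families may stop coming once the heel is better, or leave because it is not. The document does not say so; this is an assumption. It could also differ by arm, since the Conclusion acknowledges that patients are unblinded and that the footwear factor sets an active condition against an inactive one. Pain scores would then be missing for reasons tied to their own values. The Analysis section applies generalised estimating equations (GEE) without imputation to the secondary outcomes. An ordinary unweighted GEE does not in general correct for missingness that depends on the unseen score. Scores not collected at the time cannot be retrieved later.

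**Working it through.** **What can be recovered.**

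| Measure | Needs an examiner? | In the fallback now? | Could be added? |
|---|---|---|---|
| Oxford questionnaire | No | Yes | – |
| Faces, at rest | No | No | Yes |
| Faces, during activity | No | No | Yes |
| Faces, two hours after activity | No | No | Yes |
| Faces, on palpation | Yes | No | No |
| Lunge Test | Yes | No | No |

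So 3 of 4 pain ratings (75%) could use the existing route.

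**Is there a figure in the plan for missed visits?** The Sample size section has one related number, 15% for drop-outs and incomplete assessments. It reproduces the total: 108 × 1.15 = 124.2, stated as 124. But it inflates a calculation for the Oxford questionnaire, the outcome that already has postal and telephone recovery. It may therefore be loss after recovery, and it includes drop-outs who may return nothing. It is not a missed-visit rate.

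**Counts over an assumed range.** Let d be the share of the 124 children who miss a given visit and are not rescheduled. Ratings lost per visit = 4 × 124 × d; ratings within reach = 3 × 124 × d.

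| d (assumed) | Children | Ratings lost | Within reach at most |
|---|---|---|---|
| 5% | 6.2 | 24.8 | 18.6 |
| 15% | 18.6 | 74.4 | 55.8 |
| 30% | 37.2 | 148.8 | 111.6 |

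The last column assumes that every contacted family replies. At d = 15% and an assumed reply rate of 50% to 80%, 27.9 to 44.6 ratings per visit would be regained.

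**Bias illustration (all inputs assumed).** Bias in an arm's observed mean = fraction missing × (observed mean − mean of the missing). Suppose non-attenders score 2 points lower on the seven-point scale, with non-attendance of 10% in one arm and 20% in the other.

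- As written: 0.10 × 2 = 0.2 and 0.20 × 2 = 0.4. Bias in the contrast: 0.4 − 0.2 = 0.2 points.
- With a random half of non-attenders recovered: 0.05 × 2 = 0.1 and 0.10 × 2 = 0.2. Bias in the contrast: 0.1 points.
- Refinement: recovered children pull the observed mean down, so the gaps become 2 × 0.90/0.95 = 1.895 and 2 × 0.80/0.90 = 1.778. The arm biases are 0.05 × 1.895 = 0.095 and 0.10 × 1.778 = 0.178, a contrast bias of 0.083. About 0.1 is a fair summary.
- With equal non-attendance and an equal gap in both arms, the contrast bias is zero and only precision is lost.

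**The case against.** The case for leaving the plan alone is reasonable. The Faces scale is secondary, and keeping the fallback short to protect the primary outcome is a defensible priority. The document contradicts nothing here, and the primary analysis and sample size stand. The scale is described as a verbal rating, with no evidence for postal or telephone use. The call is reached only when the envelope has not come back, so the sheet may not be to hand. All of this stands. It makes the change optional in rank and shapes how it should be made, but it does not show that the pain data are safe.

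Three stronger readings are tempting and are not supported:

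- A reader might infer that every missed appointment loses the pain data. It does not: reminder, tolerance window and rescheduling call come first, and a rescheduled visit can collect everything. The loss arises only when rescheduling fails.
- A reader might infer that the disability and pain analyses would rest on different children. The Analysis section says participants with gaps are not dropped, so a child who misses one visit still contributes the attended visits to both. The analyses differ mainly in visits; they differ in children only where a child attends no follow-up yet returns an Oxford form.
- A reader might apply the 15% to each visit and quote a number of visits with Oxford but no Faces data. That number cannot be derived, because the 15% may already be net of recovery.

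The Analysis section's statement that GEE stays unbiased even when data are missing not at random is a separate matter. It cannot be relied on as a safeguard here, but it does not make this point weightier.

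**Conclusion.** The point holds in limited form. Once rescheduling has failed, the plan as written obtains no pain data for that visit even from families who reply, although three of the four ratings could be had by the same route. This is what the Procedure section states, not detail lost in condensing: it sets out the steps and names the instrument.

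The consequence is confined to the secondary pain analysis: some loss of precision and, if attendance depends on pain differently by arm, some bias. On the assumed inputs the bias is 0.2 points, of which recovering half the missed visits removes about 0.1. The document supports neither the 2-point gap nor the 10% and 20% rates, so this shows scale and is not an estimate. If families left because of persisting pain, the sign would reverse. It is a low-cost improvement, not a flaw in the primary comparison.

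**What to change.** In the Procedure section, extend the fallback as follows:

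- Post a sheet with the three self-report Faces ratings (at rest, during activity, two hours after activity) in the same reply-paid envelope, placed after the Oxford questionnaire so that the primary outcome keeps priority.
- In the telephone call already planned, offer those three ratings after the Oxford items, using the posted sheet.
- State that palpation pain and the Lunge Test remain clinic-only.
- Record for each visit whether ratings were made in clinic, by post or by telephone, so that a mode difference can be examined.

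The cost is one extra page and a slightly longer call. The downsides are a possible mixed-mode difference and a somewhat longer form. The sample size does not change.
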